**Subsidiary hypotheses:**

- 1) Hearing threshold will correlate with inflammatory biomarkers, Tumor Necrosis Factor-alpha (TNF- $\alpha$ ), InterLeukin-6 (IL-6) or C-Reactive Protein (CRP)**
  - Hearing threshold at baseline will correlate with levels of inflammatory biomarkers at baseline.
  - The trajectory of change in hearing threshold from baseline through to Year 3 will correlate with levels or change from baseline of inflammatory biomarkers at Year 3.
  - Slowing of the rate of change in hearing threshold in the aspirin group will be associated with reduction of key inflammatory biomarkers.

*The basis of this hypothesis is that an increase in plasma inflammatory biomarkers regularly accompanies old-age, presumably reflecting low-grade inflammation. With increasing age, the stria vascularis of the middle ear undergoes changes compatible with damage from an inflammatory and/or vascular degenerative process.*

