**Relationship to ASPREE trial**

ASPREE (ASpirin in Reducing Events in the Elderly) is a 5 year RCT comparing low-dose aspirin (daily slow release 100mg enteric coated) with placebo in 19,000 community-dwelling adults aged  $\geq 70$  years. The primary outcome is disability-free survival, in relation to physical disability and dementia. ASPREE participants are free of previous cardiovascular disease or stroke, dementia and other severe illness at trial entry. Although ASPREE has been funded by the US National Institutes of Health, the majority of the trial is in Australia with 16,500 participants and 2,500 in the US. At present, >13,700 Australian participants have been recruited. Recruitment will be completed by late 2014, with follow-up concluding by late 2017. Infrastructure, recruitment, data collection, follow-up and participant retention methods are well-established. Additional benefits for ASP-HEARING include access to comprehensive socio-demographic data, clinical history, significant clinical events (adjudicated endpoints), measures of activities of daily living, cognitive assessment, cardiovascular events, depression, other co-morbidities, medications and hospitalisations in the ASPREE cohort.

*Recruitment:* Participants are selected from general practices and undergo phone screening to assess suitability. Potential participants attend a baseline examination for testing and distribution of run-in (placebo) medication. Eligible participants attend further testing and are randomised to either aspirin or placebo at one month. The majority agree to provide blood and urine specimens which are stored for later biomarker and genetic analysis. ASPREE participants are telephoned regularly to support compliance. Evidence of major clinical events is collected from medical records and categorised by blinded outcomes committees.

*Inclusion criteria:* persons aged  $\geq 70$  years of age, who are English language competent, community dwelling, physically capable of regularly attending their GP, and providing informed consent.

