**ASP-HEARING STUDY PLAN**

**1. RECRUITMENT:** All newly enrolled ASPREE participants in 2014 will be invited at their baseline visit to enter ASP-HEARING, regardless of existing hearing impairment. Recruitment to

ASP-HEARING is during the final phase of ASPREE's recruitment in 2014, funded by Monash University, and it is anticipated that 1,800-2,100 of the remaining ASPREE trial recruits will consent to participate.

**2. HEARING MEASURES:** Hearing tests will be conducted without hearing aids. Any aids will be turned off and removed after testing instructions are heard and understood. Previously unknown hearing impairment will be advised to the participant's GP.

**2.1 OTOSCOPY** will be performed at the outset of the hearing evaluation. If the eardrum is occluded, the participant and their GP will be informed. Responsibility for management of any obstruction will rest with the GP. The participant will return for hearing reassessment following management of the obstruction, if this is initiated promptly within two months of randomisation.

**2.2 AUDIOMETRY AIR and BONE CONDUCTION TESTS:** In order to test the main hypothesis, hearing acuity will be tested at baseline and annually for the three years of ASP-HEARING. Pure Tone Audiometry: portable Interacoustics AD226 audiometers with ER3A inserts and sound-attenuating ear muffs, will be used to obtain air-conduction thresholds in both ears at standard octave frequencies (0.25, 0.5, 1, 2, 4, and 8 kHz). A pure tone average of air conduction thresholds at 0.5, 1, 2, and 4 kHz in the better ear will be the summary measure of hearing used in our analyses, as per the definition of hearing deficit used by the World Health Organization. (52) A bone conduction test will be performed on the better ear using two frequencies, 1 kHz and 4 kHz. This will enable distinction of age-associated sensorineural hearing loss from conductive loss – the latter irrelevant to this study. Audiometric equipment for baseline measures has been purchased with assistance from Monash University. Over the 3-year study period, even subtle changes in hearing threshold will be measureable in all participants, including any deterioration that is imposed on hearing impairment at baseline.

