**2.3 SPEECH IN NOISE TEST:** The Listening in Spatialised Noise-Sentence Test (LiSN-S) (53) assesses the ability to understand speech in the presence of spatially-separated, competing talkers. A simple repetition response assesses a listener's speech reception threshold for target sentences within background noise. Speech discrimination is affected both by cochlear loss and by the presence of certain central auditory processing disorders, (54) and together with the pure tone results the LiSN-S will help this distinction to be made. This test will provide us with a vital measure of functional hearing, the Speech Reception Threshold in noise (SRTn).

**2.4 HEARING HANDICAP AND NOISE EXPOSURE QUESTIONNAIRES:** The 10 item Hearing Handicap Inventory for the Elderly (HHIE-S) (55) and the 11 item Baltimore Longitudinal Study of Aging Self-Reported Hearing and Noise Exposure Questionnaire (56) will be administered to provide information on hearing history, noise exposure, use of hearing aids and perceived hearing handicap. This will also assist in determining the extent to which previous noise exposure contributes to hearing thresholds.

**3. INFLAMMATORY BIOMARKERS:** To test subsidiary hypothesis 1, inflammatory biomarkers IL-6, CRP and TNF- $\alpha$  will be measured in blood samples taken at baseline and change in these biomarker levels will be determined from levels measured in 3-year bloods collected by the ASPREE Healthy Ageing Biobank.

**4. RETINAL VESSEL IMAGING (RVI):** To test subsidiary hypothesis 2, retinal photography will be used to measure retinal vessel diameters, branching and vessel wall opacity and tortuosity. We are seeking evidence of microvascular changes which may be a causal factor in presbycusis. RVI provides a convenient and accessible measure of blood vessel change. ASP-HEARING will take advantage of RVI equipment currently used by ASPREE's Age Related Macular Degeneration (AMD) sub-study.

**5. COGNITIVE FUNCTION TESTS:** To test subsidiary hypothesis 3, results from annual cognitive function assessments will allow determination of associations and causal relationships

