| Hearing Questionnaires b                                                                                                                                                                                                                                                                                                                                                                                                               | X    | X    | X    | X    |                                       |
| Retinal Vascular Imaging                                                                                                                                                                                                                                                                                                                                                                                                                          | X    | X    | X    | X    |                                       |
| Cognitive Function Tests c                                                                                                                                                                                                                                                                                                                                                                                                             | X    | X    | X    | X    |                                       |
| Inflammatory Biomarkers                                                                                                                                                                                                                                                                                                                                                                                                                           | X    |      |      | X    |                                       |

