**POWER AND SAMPLE SIZE CALCULATIONS:** To address the primary hypothesis, 1800 participants provide 80% power to detect a difference in average hearing level/threshold (HL) change from a mean annual dB HL increase of +0.86 in the placebo group to a mean annual dB HL increase of +0.64 in the aspirin group (assuming SD of 1.64 dB HL for changes in HL over 3 years). This calculation is based on the background increase per annum of HL in Australians aged ≥75, with an average Pure Tone Audiometry 0.5, 1, 2, 4 kHz trajectory of +0.86 dB.(8)

**STATISTICAL ANALYSIS:** A linear mixed model with HL at years 0, 1, 2, and 3 as the repeatedly measured outcome will be used for all analyses equivalent to a model for follow-up HL measures that adjusts for baseline HL. (57) For the main hypothesis, the model will include an interaction term between treatment group (placebo/aspirin) and time since randomisation; the estimated interaction effect will summarise the evidence for/against this hypothesis. This model assumes a missing at random (MAR) mechanism for any unobserved HL values. Secondary analyses will include a sensitivity analysis of findings to the MAR assumption, enabling exploration of whether differential drop-out between groups during the follow-up period affects the estimates of treatment effect.

The same model structure will be used to assess evidence for the subsidiary hypotheses. Separate analyses will be undertaken for the inflammatory biomarkers: TNF- $\alpha$ , IL-6 and CRP, for the retinal microvascular change indicators (retinal arteriolar, venular calibre and focal arteriolar narrowing), and for cognitive impairment as measured by 3MS noting that each of these measures is on a continuous scale. For example, for TNF- $\alpha$ , the model will be extended to include the baseline TNF- $\alpha$  values and its corresponding parameters relating it to HL at baseline will assess evidence for cross-sectional association at baseline. For assessing association of biomarker changes with progression of HL, the model will be further extended to include the time-dependent TNF- $\alpha$  change from baseline as an explanatory variable. For assessing whether TNF- $\alpha$  mediates an aspirin-induced

slowing of HL, the model will be extended again to include an interaction between treatment group (placebo/aspirin) and the time-dependent TNF- $\alpha$  change from baseline.

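### The biomarker progression and mediation models need a marker change at every hearing visit, but the markers are measured only at baseline and Year 3

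*Protocol*

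**What the plan says.** The Statistical Analysis paragraph of the protocol sets one outcome structure: "A linear mixed model with HL at years 0, 1, 2, and 3 as the repeatedly measured outcome will be used for all analyses". This fits the audiometry schedule in section 2.2, where "hearing acuity will be tested at baseline and annually for the three years of ASP-HEARING".

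The same paragraph builds the marker analyses in three steps, with TNF-α as the worked example:
- Baseline marker values are added, for the cross-sectional association.
- For progression, "For assessing association of biomarker changes with progression of HL, the model will be further extended to include the time-dependent" change in the marker since baseline.
- For mediation, "the model will be extended again to include an interaction between treatment group (placebo/aspirin) and the time-dependent" change.

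Section 3 (Inflammatory Biomarkers) says that the three markers "will be measured in blood samples taken at baseline and change in these biomarker levels will be determined from levels measured in 3-year bloods". In the timeline table, the "Inflammatory Biomarkers" rows for ASP-HEARING and for the Biobank sub-study are both marked in 2014 and 2017 and blank in 2015 and 2016.

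Subsidiary hypothesis 1 itself asks for less than the model does: the course of hearing to Year 3 "will correlate with levels or change from baseline of inflammatory biomarkers at Year 3". That is one value per person.

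**The concern.** A linear mixed model can use a participant whose outcome is missing at some visits. It cannot use a visit at which a covariate is missing unless a rule supplies the value. Here the marker change is missing at Years 1 and 2 for everyone, by design, and no rule is given. The assumption in the Statistical Analysis paragraph is about unobserved HL values and does not address unobserved markers.

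Two things are at stake for the progression and mediation parts of hypothesis 1. Annual hearing tests are collected and then left unused, although the hypothesis is about a trajectory. The coefficients of interest also come only from people who reached Year 3 and gave blood. The section on the relationship to ASPREE says of specimens: "The majority agree to provide blood and urine specimens which are stored for later biomarker and genetic analysis". Some missing samples should therefore be expected even apart from drop-out.

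**Working it through.** The protocol gives no figure for the marker models, so there is none to reproduce. The planned size of 1,800 enters only as a count.

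**Which visits have both quantities**

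| | Year 0 | Year 1 | Year 2 | Year 3 |
|---|---|---|---|---|
| HL (section 2.2; Statistical Analysis) | yes | yes | yes | yes |
| IL-6, CRP, TNF-α (section 3; timeline) | yes | no | no | yes |
| Marker change since baseline | 0 for all | undefined | undefined | observed if sampled |

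The parent trial's annual cardiovascular biomarkers do not fill the gap. The table footnote lists lipids, haemoglobin, glucose, creatinine and urine albumin:creatinine ratio.

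**Rows available**

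- Planned: 1,800 × 4 = 7,200 rows, of which 1,800 × 3 = 5,400 are follow-up.
- With a defined change: at most 1,800 × 2 = 3,600 (50%), of which 1,800 of 5,400 follow-up rows (33%).

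The protocol gives no proportion without a Year 3 sample, so a range is assumed:

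| Assumed without Year 3 sample | Rows, model as written | Follow-up rows | Share of 5,400 |
|---|---|---|---|
| 0% | 3,600 | 1,800 | 33% |
| 10% | 1,800 + 1,620 = 3,420 | 1,620 | 30% |
| 20% | 1,800 + 1,440 = 3,240 | 1,440 | 27% |
| 30% | 1,800 + 1,260 = 3,060 | 1,260 | 23% |

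**Where the coefficient comes from.** The change is zero for everyone at Year 0, so only Year 3 rows carry variation in it. One simulated data set illustrates this (1,800 participants, an assumed 20% without a Year 3 marker, random-intercept model). The model kept 3,219 of 7,200 rows, all at Years 0 and 3. The marker-change coefficient was 0.486 (SE 0.083) with everyone included and 0.485 (SE 0.083) among those with a Year 3 sample. The others added nothing material to that term. Missingness was random in this simulation, so it says nothing about the size of any selection bias.

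**Precision for those retained.** The error variance of a person's slope is σ²/Σ(t − t̄)², with t̄ = 1.5 in both cases.

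- Visits 0, 1, 2, 3: 2.25 + 0.25 + 0.25 + 2.25 = 5.0.
- Visits 0, 3: 2.25 + 2.25 = 4.5.
- Ratio: 5.0/4.5 = 1.11, or 11% more error variance.

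True variation in slopes between people adds the same amount to both variances, so 11% is the most the total slope variance can rise.

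**Rows with one change value per person.** Everyone with a Year 3 sample brings all four HL visits. In the simulated data that is 4 × 1,419 = 5,676 rows, against 3,219.

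**The case against.** The strongest reply is that TNF-α is only an example of a template shared with measures taken every year, and that coding it for a marker with two time points belongs in a SAP, which is not at hand. Loss of the Year 1 and 2 rows is also an inference from fitting the model as written; the protocol does not say that they will be dropped. That much stands. But the protocol names a specific covariate that its own schedule cannot supply, which goes beyond an omitted detail. Interpolation or carrying values across would avoid the deletion, but neither is specified, and no observed Year 1 or 2 values exist to inform or check it.

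It is also fair that regressing on Years 0 and 3 still relates 3-year hearing change to 3-year marker change. The hypothesis is tested, with less information.

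A reader might infer more than the documents support:
- *That people without a Year 3 sample are lost to hypothesis 1 altogether.* Its first part is a baseline association, to which anyone with baseline blood contributes. Such people also keep a baseline row in the extended models.
- *That the missing-at-random assumption fails for hypothesis 1 as a whole.* The baseline part is untouched, and the protocol never claimed that the assumption covers markers.
- *That the results will be biased.* Selection is possible, but nothing in the protocol allows its direction or size to be estimated.

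**Conclusion.** The point holds for the progression and mediation models of subsidiary hypothesis 1. The stated covariate is undefined at two of the three follow-up visits. As written, at most half of the planned HL rows can be used, and the marker-change and treatment-by-change coefficients are in effect complete-case on the Year 3 sample. This rests on the model being fitted literally, with no rule for filling Years 1 and 2. The proportions without a sample are assumptions.

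The primary treatment-by-time analysis and the baseline cross-sectional analysis are not affected. Retinal imaging and 3MS are planned annually, so the time-dependent form works for them. The precision cost is small and any selection effect is unquantified. Severity is moderate: a secondary analysis that should be reworded, with no bearing on the trial's main conclusion.

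**What to change.** For IL-6, CRP and TNF-α, replace the time-dependent term with the single Year 3-minus-baseline change as a person-level covariate, interacting with time. For the third step, use treatment × change × time, with its lower-order terms, in place of treatment × time-dependent change. This matches the hypothesis as stated and uses all four HL measurements. Keep the time-dependent form for retinal imaging and 3MS.

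This still needs a Year 3 sample, so it recovers Years 1 and 2 but does not remove the selection. Multiple imputation of missing Year 3 markers can be added as a sensitivity analysis, with its own missing-at-random assumption stated. Because the marker change is completed only at the last hearing visit, report the results as association and not as temporal mediation.

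The cost is wording in the protocol or SAP, with no new assays or visits. The downside is that marker change is treated as one 3-year summary, which is also used to explain hearing at Years 1 and 2.

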**AIMS AND HYPOTHESES**

**Main aim:** To determine whether low dose aspirin decreases progression of age-related hearing loss.

**Main hypothesis:** Low dose aspirin will reduce progression of age-related hearing loss.

*The basis of this hypothesis is that aspirin is an anti-inflammatory agent, which even in low dose may produce significant suppression of plasma biomarkers of inflammation. If a low-grade inflammatory process, either directly or via microvascular change, contributes to the pathogenesis of ARHL, then aspirin will slow the progression of hearing loss.*

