## 2) Hearing threshold will correlate with retinal microvascular changes.

- Hearing threshold at baseline will correlate with the extent of retinal microvascular changes at baseline.
- The trajectory of change in hearing threshold from baseline through to Year 3 will correlate with progression of retinal microvascular changes across the study.
- Slowing of rate of change in hearing threshold in the aspirin group will be associated with slower progression of retinal microvascular changes.

*The basis of this hypothesis is that age-related changes in the microvasculature in the stria vascularis may be a primary cause of ARHL. The retina enables quantitative imaging of the microvasculature. Such changes may then reflect vascular changes in the cochlea.*

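### The term prescribed to test mediation, a treatment-by-marker-change interaction, measures effect modification, and no planned model estimates aspirin's effect on the markers

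*Protocol*

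**What the plan says.** The Statistical Analysis paragraph of the Protocol (ASP-HEARING Study Plan) fixes the outcome first: "A linear mixed model with HL at years 0, 1, 2, and 3 as the repeatedly measured outcome will be used for all analyses". For the secondary questions it adds: "The same model structure will be used to assess evidence for the subsidiary hypotheses". It names the three inflammatory biomarkers, the retinal measures and 3MS, and works through TNF-alpha as the example in three nested steps.

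1. Baseline TNF-alpha enters the model, for cross-sectional association.
2. For association with progression, "the model will be further extended to include the time-dependent" change in TNF-alpha.
3. "For assessing whether TNF- $\alpha$ mediates an aspirin-induced" slowing, the prescribed term is: "slowing of HL, the model will be extended again to include an interaction between treatment group (placebo/aspirin) and the time-dependent" change in TNF-alpha.

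The hypotheses these steps serve are the third bullets of the subsidiary hypotheses. For inflammation: "Slowing of the rate of change in hearing threshold in the aspirin group will be associated with reduction of key inflammatory biomarkers". For microvessels: "Slowing of rate of change in hearing threshold in the aspirin group will be associated with slower progression of retinal microvascular changes". The basis given for the main hypothesis is the same mechanism: "If a low-grade inflammatory process, either directly or via microvascular change, contributes to the pathogenesis of ARHL, then aspirin will slow the progression".

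**The concern.** Mediation has two parts: aspirin must change the marker, and that change must carry some of the treatment effect on HL. Step 3 estimates neither. Its coefficient compares the HL-on-marker slope in the aspirin arm with that in the placebo arm, so it answers a question about modification while the text calls it mediation.

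The first part, aspirin to marker, is estimated nowhere in the stated plan, because every model has HL as its outcome. That path is not a formality. The Background describes some trials in which aspirin lowered inflammatory markers and five in which it did not, and calls the effect modest and variable.

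What is at stake is the mechanistic conclusion. Read as the test of mediation, step 3 would usually pass over a true mediator and could credit a marker that aspirin never moved. A statistical analysis plan that follows the Protocol would inherit the mismatch.

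**Working it through.** **Step 1. What the coefficient measures.** Let T be treatment (1 = aspirin), M the marker change in SD units and Y the HL change.

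- M = aT + error
- Y = cT + bM + gTM + error

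With g = 0 the indirect effect is ab and the total effect is c + ab. Step 3 tests g. Under linear mediation g = 0 for any a and b, so the test rejects at its alpha level however large ab is. If a = 0 there is no indirect effect, yet g may be non-zero and the test may reject. This needs no assumed numbers.

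**Step 2. The plan's own figure, to set the scale.** The Protocol gives no figure for the mediation analysis. For the primary hypothesis it states 1,800 participants, 80% power, annual increases of 0.86 and 0.64 dB, and an SD of 1.64 dB. I assume a two-sided 5% test and 1:1 allocation, which are not stated.

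- Difference: 0.86 − 0.64 = 0.22 dB per year.
- n per arm = 2 × (1.960 + 0.842)² × 1.64² / 0.22² = 873 after rounding up, or 1,746 in total.
- Power with 900 per arm: SE = 1.64 × √(2/900) = 0.0773; 0.22 / 0.0773 = 2.85; Φ(2.85 − 1.96) = 81%.

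The stated figure is reproduced when 1.64 is paired with the annual difference, so that scale is used below.

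**Step 3. Illustrative simulation.** N = 1,800, 4,000 runs per scenario, one marker change and one annualised HL change per person, residual SD 1.64. Path sizes are assumptions, because the Protocol gives none. The total effect is −0.22 in the first four rows (for example −0.5 × 0.44 = −0.22; −0.25 × 0.44 − 0.11 = −0.22). In the last row −0.22 is the effect at zero marker change.

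| Scenario | a | b | c | g | Interaction significant | Both paths significant |
|---|---|---|---|---|---|---|
| Full mediation | −0.5 | 0.44 | 0 | 0 | 5.2% | 100% |
| Full mediation, smaller a | −0.25 | 0.88 | 0 | 0 | 5.4% | >99.9% |
| Half mediated | −0.25 | 0.44 | −0.11 | 0 | 4.9% | >99.9% |
| Direct effect only | 0 | 0.44 | −0.22 | 0 | 5.6% | 5.2% |
| Modification, no mediation | 0 | 0.44 | −0.22 | 0.3 | 97.1% | 4.9% |

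A repeated-measures version (HL at years 0 to 3, random intercept and slope, treatment-by-time kept, 1,000 runs, variances and paths again assumed) gave the same pattern. The interaction was significant in 4.8% to 5.0% of trials under full or half mediation, and in 99.5% under modification alone. With the marker measured only at years 0 and 3, the rates were 4.0% to 5.6% and 94%.

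**Step 4. How far the rates depend on the inputs.** The 5% rate follows from step 1 and does not depend on a or b. The rates near 100% do. If aspirin shifts the marker by only 0.1 SD, then SE = √(2/900) = 0.047, 0.1 / 0.047 = 2.12, and Φ(2.12 − 1.96) is about 56%. The joint test could then reach at most about 56%. The 97% depends likewise on the assumed g = 0.3.

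**Step 5. Marker timing.** The Inflammatory Biomarkers section and the timeline table give biomarkers at baseline and year 3 only. A time-dependent change is then 0 at year 0 and d at year 3. Multiplied by time it is 0 and 3d, exactly three times the change itself. A marker-change-by-time term cannot be separated from the marker change for TNF-alpha, IL-6 or CRP.

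**The case against.** **No decision rule is stated.** For the main hypothesis the Protocol names the quantity that carries the evidence. For the mediation step it says only that a term is added. A treatment-by-mediator interaction is also a legitimate part of a causal mediation model, and the estimand could be left to a statistical analysis plan. It is true that including the term is not in itself an error. But step 3 is the only analysis offered for mediation, and it names no indirect effect and no marker model. The Protocol has fixed the question and a term that does not answer it.

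**The nested models already hold most of the ingredients.** The treatment-by-time effect without the marker comes from the base model, and with the marker from step 2. This stands. A reader might infer that the trial cannot show whether aspirin works through inflammation or microvessels. The documents do not support that: the markers are measured in both arms and the question can be recovered. The limit lies in the prescribed test.

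**The hypotheses speak of association.** This is also true. Mediation is named only in the Statistical Analysis paragraph, and arm-specific slopes address one literal reading of the third bullets. It does not repair the sentence that does name mediation.

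**The rates rest on chosen inputs.** A reader might take figures such as 97% or 100% as properties of this trial. They are not. The Protocol gives no path sizes, and its only stated SD is 1.64 dB.

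**Conclusion.** The sentence is wrong as written. The prescribed coefficient measures effect modification, rejects at about alpha under linear mediation, and can reject when aspirin does not change the marker. The aspirin-to-marker path is absent from the stated models. The argument assumes a linear mediation structure; the simulated rates also assume path sizes and an SD, and are illustrative only.

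The reach is limited to the subsidiary mechanistic hypotheses. A reader might infer that the main conclusion is compromised, but the primary treatment-by-time comparison does not use this term, and the sample size and data collection are unaffected.

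Even a correct analysis will rest on assumptions. The single post-baseline biomarker value coincides with the final HL measurement, so temporal order and the absence of unmeasured mediator-outcome confounding cannot be read off the data.

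**What to change.** Replace the mediation sentence before unblinding, since a later change would look post hoc. For each candidate mediator:

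- **(a)** Model the marker change as the outcome, adjusted for the baseline marker, and report the aspirin effect on it.
- **(b)** Fit the HL model with and without the marker change, adjusting for baseline marker, baseline HL and measured common causes. For TNF-alpha, IL-6 and CRP, relate year-3 marker change to year-3 HL and add no marker-change-by-time term.
- **(c)** Report the indirect effect with a bootstrap confidence interval. Keep the treatment-by-marker interaction only as a check, or as a component of that model.

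State that the year-3 biomarker is concurrent with the final HL, and that temporal order and no unmeasured mediator-outcome confounding are assumptions.

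The cost is revised wording and a little more analysis. No new data are needed.
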